### Recruitment

The study took place in 11 ICUs, which had been selected based on the interest expressed by local teams in post-ICU follow-up, for their capacity to recruit patients and to handle the restraints of an RCT. A research assistant was available at every participating center to screen patients for inclusion. The steering committee met monthly. A centralized phone and email center answered participating center questions regarding patient eligibility or management during the entire trial period. A monthly newsletter was circulated, informing participating centers of the number of patients included, main study constraints, and any protocol modifications (Table 2).

**Table 2 table2:** Number of patients included and participating centers and inclusion rate.

Evaluation	Values required
Number of patients to be included	546
Number of centers	11
Number of months	54
Number of patients per month per center	1

### Assignment of Interventions: Allocation

#### Sequence Generation

The randomization list, generated by an independent statistician, was balanced between arms. Randomization was stratified by center using a permuted block of unrevealed size randomization. As critical severity could potentially impact the rate and intensity of psychological, cognitive, and physical impairment, stratification was made on this basis.

#### Concealment Mechanism

Randomization and concealment were ensured by using a secure dedicated web-based system accessible at each study center and managed by the clinical research unit (CRU), which had no role in patient recruitment.

#### Implementation

The allocation sequence was generated by the study statistician. Patient enrollment was established by the participating center investigator.

### Assignment of Interventions and Blinding

The outcome assessor assessing the EQ5D by phone was blinded. Neither the participants nor the investigators (ie, ICU physicians, psychologists, and social workers) were blinded for patient assignment to one of the trial groups. The procedure for unblinding was not planned as the intervention was considered safe.

### Data Collection and Management

#### Plans for Assessment and Collection of Outcomes

At inclusion, baseline characteristics were systematically collected by the center investigator as follows: demographic and anthropometric data; location prior to ICU admission (community, hospital, or long-term facility); pre-existing comorbidities using Knaus, McCabe, and Charlson scores; date and time of ICU admission; and severity of critical illness at ICU admission using the Simplified Acute Physiology Score (SAPS-II) and the Sequential Organ Failure Assessment (SOFA) score [42,43]. In addition, body weight, height, vital signs, MRC sum score [9], the Barthel index [44], IADL scores [45], MMS [46], HAD-S [47], IES-R [48], and the social questionnaire were collected for all participants. Patients’ were also asked to score their QoL 3 months before ICU admission, using the EQ5D tool. The functional and psychological scores were completed by the patients, with help from the research technician. The MRC sum score and MMS were assessed by the ICU physician in charge of the patients. This assessment ensured that both the functional, cognitive, psychological, and social status and pre-ICU QoL were comparable between the 2 trial groups. Finally, blood samples were taken for standard biological tests, including blood cell count; biochemistry; and plasma levels of C-reactive protein, pre-albumin, albumin, and thyroid hormones.

At time of ICU discharge the duration of MV, need for tracheostomy, and length of ICU stay were also recorded.

Intervention group patients were seen by the ICU physician, the psychologist, and the social worker before ICU discharge (month 0) and at 3 months, and eventually at 6 months by the follow-up team. The psychologist and social worker had access to the scores and questionnaire completed by the patients at inclusion. At 3 and 6 months, the MRC sum score, Barthel index, IADL, MMS, HADS, and IES-R were collected as well as the social questionnaire and results of the biological tests.

At 12 months, the EQ5D (ie, primary endpoint) was assessed on the phone by a blinded assessor. All patients were seen by the ICU physician, psychologist, and social worker. The MRC sum score, Barthel index, IADL, MMS, HADS, and IES-R, together with the 36-item Short Form (SF-36) for assessing QoL and the social questionnaire, were collected. Standard biological tests were performed at 12 months.

The reason for failure to attend the planned consultation was recorded by the research technician via telephone. The date and cause of readmission to hospital and death were also documented. The number of consultations with the general practitioner or any other specialist was recorded.

#### Plans to Promote Participant Retention and Complete Follow-up

Each month, the participating teams were informed of the course of the study and reminded of the main elements of the trial, notably concerning the organization of the follow-up consultation.

#### Data Management

Data management and statistical analysis were performed independently of the sponsor and of investigators by the CRU (Unité de Recherche Clinique, Hôpital Ambroise-Paré, Boulogne-Billancourt, France). Data entry was performed by the investigator at enrolling sites using a web-based data entry system.

An electronic case report form (eCRF) was developed by the CRU using dedicated software (CleanWeb) to facilitate data control and monitoring. Each patient was assigned a unique study ID that was used to index the eCRF and related study documents. It captured data from each included patient.

All information required by the protocol had to be entered in the eCRFs. Data were recorded in the eCRF as and when they were obtained. Any missing data had to be coded. In-built consistency checks instantly verified the coherence of data.

Data monitoring was performed by the sponsor (Direction de la Recherche Clinique et de l’Innovation de l’Assistance Publique – Hôpitaux de Paris [DRCI AP-HP]). This project was classified as interventional with potential risks based on the AP-HP risk level classification, meaning that a high level of monitoring is necessary for determining whether centers adhere to the protocol and procedures, for checking for eCRF completeness, for ensuring patient safety (adverse event/serious adverse event), and for follow-up in accordance with the applicable regulations. A clinical research associate (CRA) appointed by the sponsor is responsible for timely completion of the study and for collecting, documenting, recording, and reporting all handwritten data, in accordance with the standard operating procedures applied within the DRCI APHP and in accordance with Good Clinical Practices as well as the statutory and regulatory requirements. During these visits, the following elements were reviewed:

Written consent.Safety and rights of participants being protected.Compliance with the study protocol and with the procedures defined therein.Quality of data collected in the eCRF (accuracy, missing data, consistency of the data with the “source” documents, such as medical files, appointment books, original copies of laboratory results, etc.).Data were authentic, accurate, and complete.

The CRA systematically checked baseline characteristics, eligibility criteria, primary outcome, and serious adverse events reported in the eCRF for all study participants. In addition, for one-third of the study population, all data reported in the eCRF were validated against a patient’s original chart. Serious adverse events and major protocol violations were reported to the DRCI APHP and Comité de protection des personnes (CPP; Ethics Committee).

At the end of the study, after clarification of discrepancies (data cleaning) and data validation, the database was frozen and transmitted to the statistician, following procedures established by the sponsor.

Each patient participated in the trial for 12 months. Premature study withdrawal was at the request of the patient or next of kin and their reasons were recorded in the eCRF and the patient’s medical file. Withdrawn patients were not replaced. However, patients who were lost to follow-up or did not receive the randomly assigned treatment were not considered to be prematurely withdrawn from the trial.

### Confidentiality

As for any clinical research supported by the AP-HP, processing of personal data complied with the methodological requirements for a clinical trial established by the French Data Protection Authority Commission Nationale de l’Informatique et des libertés Commission Nationale de l’Informatique et des libertés (CNIL) in January 2006 for biomedical research. During and after the clinical research, all collected data sent to the sponsor by the investigators (or any other specialized collaborators) were pseudonymized using only the participant’s initials. Under no circumstances the names and addresses of the participants involved had been shown. Only the participant’s initials and an encoded number specific to the study indicating the order of enrollment were recorded. Moreover, all nominal data were erased on the copies of the source files that were used for research documentation.

### Plans for Collection, Laboratory Evaluation, and Storage of Biological Specimens for Genetic or Molecular Analysis in This Trial/Future Use

No genetic or molecular analyses were planned.

### Statistical Methods

#### Statistical Methods for Primary and Secondary Outcomes

The 1-year survival rate without major deterioration in QoL (main endpoint, defined as reporting of death or a severe to extreme problem” level in 1 of the 5 dimensions studied) will be compared between both arms using a piecewise exponential model considering any censorship and the repeated nature of observations, prohibiting the use of conventional methods of analysis of censored data. This analysis will be adjusted for age and severity of critical illness (according to SOFA grading), and the center will be considered as a random effect. In addition, 2 analyses will be performed, according to age category (with cut-off at 65 years) and severity of critical illness (with a cut-off at the median value).

Binary outcomes will be analyzed using logistic regression. Absolute risk reductions will be obtained using a binomial model with identity link [49]. For time-to-event outcomes, Kaplan-Meier survival curves or cumulative incidence curves will be estimated, and the intervention effect will be analyzed using the Cox proportional hazards regression. Mixed linear regression will be used for continuous outcomes, possibly after variance-stabilizing transformation. All tests will be 2-sided at a .05 significance level.

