**Methods:**

Patients were randomized to the control or intervention arm. In the intervention arm, multidisciplinary follow-up involved medical, psychological, and social evaluation at ICU discharge and at 3, 6, and 12 months thereafter. In the placebo group, patients were seen only at 12 months by the multidisciplinary team. Baseline characteristics at ICU discharge were collected for all patients. The primary outcome was QoL at 1 year, assessed using the Euro Quality of Life-5 dimensions (EQ5D). Secondary outcomes were mortality, cognitive, psychological, and functional status; social and professional reintegration; and the rate of rehospitalization and outpatient consultations at 1 year.

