#### Intervention Description

Patients were included at time of their discharge from the ICU either to home or to another department of the same or another hospital. By convention, day 1 corresponded to the date of inclusion. The randomization was performed after the baseline assessment at the time of inclusion. The last consultation was planned at 12 months, after the simple blinded collection of the primary endpoint.

In both therapeutic groups, patients’ medical, psychological, and social scores and questionnaires were assessed at the time of inclusion and at 12 months, to evaluate whether the characteristics of the 2 therapeutic groups were comparable at baseline and to determine the respective course of post-ICU discharge impairments in both groups. The scores and questionnaires were completed by the patient alone or with the help of the research assistant. If the patient was included in the control group, the test results were sealed for disclosure at the end of the study. Test results for intervention group patients were passed to the multidisciplinary team to avoid repeating the tests.

The patients from the control group had no additional post-ICU consultation. In the intervention group, patients received a multidisciplinary consultation within the first weeks after inclusion, at 3 months, and (if necessary) at 6 months. This was a consultation with a physician, a psychologist, and a social worker. Both the physician and social worker were from the ICU participating in the trial. The ICU-referring psychologist was active in 9 centers. A psychologist was specifically recruited for performing the follow-up in the remaining 2 centers. The same multidisciplinary team was used for follow-up in each patient.

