The ICU physician consultation comprised (1) the collection of information about the current treatment, weight, vital signs, comorbidities, and symptoms; (2) the date and cause of readmission at the hospital; (3) standardized general examination; (4) functional status using the Medical Research Council (MRC) sum score for assessing muscle strength and the Barthel index and Instrumental Activities of Daily Living (IADL) scores for assessing disability; and (5) cognitive status using the Minimal Mental State (MMS) scoring system. It was recommended that the participant was followed by the same ICU physician throughout follow-up. The ICU physician could prescribe a paraclinical exploration or a treatment, but it was recommended that they referred to the patient’s general practitioner, except in the case of an emergency.

The consultation with the psychologist consisted of the collection of the Hospital Anxiety and Depression Scale (HADS) and Impact Event Scale-Revised (IES-R) scores for assessing PTSD as well as an interview during which the participant reported any psychological difficulties. The consultation with the social worker consisted of the collection of the social questionnaire response and an interview during which the patient reported about their QoL (Euro Quality of Life-5 dimensions [EQ5D]), social and professional difficulties, and needs.

In total, the medical, psychological, and social consultations took 2 h and 30 min. They were followed by a meeting between the ICU physician, psychologist, and social worker to discuss the participant’s status and requirements and to write a summary report to forward to the general practitioner.

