### Sample Size

At the time of the study design, other studies indicated that 10% of patients discharged from ICU died within the first year and 40% had a moderate to severe impairment on at least one dimension of the EQ5D [32,41].

Therefore, we estimated that at least 50% had a very poor outcome, combining death and severe to extreme impairment of at least one EQ5D dimension. [23]. The study was then powered to detect a decrease from 50% to 37% of patients with very unfavorable outcome with a power of 80% and a 2-sided 5% alpha risk, assuming this rate would be 50% in the control arm. Accordingly, the sample size was 249 patients per group. We anticipated that 20% of the patients would be lost to follow-up, so the sample size was increased to 300 per arm. The study therefore initially planned to enroll a maximal sample size of 600 patients. However, as the rate of loss to follow-up has, indeed, proved to be 10%, we decided to decrease the sample size to 520 patients. Finally, 546 patients were included. Interestingly, recent studies on comparable populations of critically ill patients showed that there was a 1-year mortality rate of between 10% and 28% [2,3,5,8,20] and that about 60% of patients had a moderate to severe impairment on at least one dimension of the EQ5D [3,10,29]. These findings suggest that our original estimation is still appropriate.

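### The primary model is justified by repeated observations, but the schedule gives no repeated EQ5D common to both arms, and the article does not settle whether intervention-only EQ5D values are used

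*Protocol article*

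**What the plan says.** All references are to the protocol article.

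- **Primary analysis** (Statistical Methods for Primary and Secondary Outcomes): the endpoint is "The 1-year survival rate without major deterioration in QoL", where failure is death or a severe to extreme level on an EQ5D dimension. The arms are compared "using a piecewise exponential model considering any censorship and the repeated nature of observations", and the article says these features rule out conventional censored-data methods.
- **Primary assessment** (Plans for Assessment and Collection of Outcomes): "At 12 months, the EQ5D (ie, primary endpoint) was assessed on the phone by a blinded assessor". Table 1 likewise places the main outcome at 12 months only, in both groups.
- **Control arm** (Intervention Description): "The patients from the control group had no additional post-ICU consultation". The abstract agrees: "patients were seen only at 12 months by the multidisciplinary team".
- **Intervention arm** (Intervention Description): "patients received a multidisciplinary consultation within the first weeks after inclusion, at 3 months, and (if necessary) at 6 months". The social worker's part of the consultation includes "an interview during which the patient reported about their QoL (Euro Quality of Life-5 dimensions [EQ5D" score. The blinding section says social workers were not blinded.
- **Instruments at 3 and 6 months** (Plans for Assessment and Collection of Outcomes): muscle strength, disability, cognitive, psychological and social measures and biology are listed. EQ5D is not.
- **Sample size**: "The study was then powered to detect a decrease from 50% to 37% of patients with very unfavorable outcome", with 249 patients per group.

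**The concern.** A time-to-event model for repeated observations needs an outcome that is observed on the same schedule in both arms. Here the only EQ5D values between randomization and month 12 would come from consultations that control patients do not have. They would be given to unblinded staff, and at month 6 only where a visit was thought necessary.

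Taken literally, the stated rationale invites those values into the primary model. A patient who is severely impaired at 3 months and recovered by 12 months would then count as a failure in the intervention arm and a success in the control arm. That could hide a real benefit or look like harm. If the values stay out, the reason given for the model has no data behind it.

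**Working it through.** **1. What the sample size assumes.** Inputs from the Sample Size section: p1 = 0.50, p2 = 0.37, power 80%, two-sided 5%. With mean proportion 0.435 and difference 0.13:

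n = [1.960·√(2·0.435·0.565) + 0.842·√(0.50·0.50 + 0.37·0.63)]² / 0.13² = (1.374 + 0.585)² / 0.0169 = 227.1, so 228 per arm.

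With continuity correction: n/4 · [1 + √(1 + 4/(n·0.13))]² = 242.2, so 243 per arm.

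The stated 249 is within 3% of 243. The design figure is a comparison of two proportions, with no repeated-measures or event-time input.

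**2. Which EQ5D values exist in each arm.**

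| Time | Control | Intervention |
|---|---|---|
| Inclusion | recalled pre-ICU value | recalled pre-ICU value |
| First weeks | none | reported to social worker, per Intervention Description |
| 3 months | none | yes per Intervention Description; absent from the list in Plans for Assessment |
| 6 months | none | same conflict, and visit only if necessary |
| 12 months | blinded call | blinded call |

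The recalled value describes the time before ICU admission, so it cannot be an outcome event. The only EQ5D after randomization that both arms share is the 12-month call.

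**3. If interim values enter: proportion counted as failed.** Assumptions not in the article: no true effect; the same prevalence of severe impairment in survivors at 3, 6 and 12 months; exchangeable within-patient correlation on a latent normal scale; deaths spread evenly over the year. The 10% mortality is from the Sample Size section. There were 400,000 simulated patients per scenario. At 40% prevalence, control failure is 0.10 + 0.90 × 0.40 = 46%. The excess in the intervention arm, in percentage points, is:

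| Correlation | Nobody attends month 6 | Everybody attends month 6 |
|---|---|---|
| 0.5 | 14.5 | 22.5 |
| 0.7 | 11.0 | 16.9 |
| 0.85 | 7.7 | 11.7 |
| 0.95 | 4.4 | 6.7 |

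At 20% prevalence and correlation 0.85, the excess is 5 to 9 points.

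**4. If interim values enter: the fitted model.** A piecewise exponential model with cuts at 3, 6 and 12 months was fitted to 400 simulated trials per scenario, with 260 per arm (half of the revised 520). Each quality-of-life event was dated at the visit that detected it. Prevalence was set so that 12-month failure is 50% (0.10 + 0.90 × 0.444), either flat or falling from 60% at month 3. Correlation was 0.6 to 0.95, and month 6 was attended by none or all.

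- No true effect: hazard ratio 1.49 to 2.88 against the intervention, with significant harm in 93% to 100% of runs.
- True fall from 50% to 37% at 12 months: hazard ratio 1.02 to 2.03, with significant benefit in at most about 1% of runs.

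**5. If only the 12-month call and deaths are used.** Both arms have the same schedule, so ascertainment does not differ by arm. The event is the composite in the Sample Size section. Every quality-of-life failure falls at month 12, and only deaths have an earlier time. Nor does censoring rescue the rationale: the missing-data section replaces each missing primary outcome by a success or a failure, which treats the endpoint as binary.

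**6. Power of a binary 12-month comparison, 50% against 37%.** 81.2% at 234 per arm (260 less 10%), 83.5% at 249, and 86.7% at 273 (half of the 546 enrolled).

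**The case against.** A reader might infer that the planned analysis will use the consultation EQ5D values and so will be biased against the intervention. The article does not say so. Table 1 and Plans for Assessment tie the primary endpoint to the blinded 12-month call, and the 3- and 6-month instrument list omits EQ5D. The better-supported reading is that interim values stay out, and the bias is then absent.

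A reader might also infer that the model misses the powered endpoint on either reading. It does not. With 12-month and death data only, the event is the powered composite. A piecewise exponential model can be fitted to it and can yield a 1-year event-free rate. The article does not commit to a hazard ratio as the reported answer.

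The size is soft as well. The article's 40% refers to moderate to severe impairment, whereas the endpoint needs severe to extreme, so no prevalence used here comes directly from the text. An interval-censored model would lessen the bias, though it would still rest on unequal schedules. A separate statistical analysis plan, not shown, may specify which observations enter.

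These points limit the finding but do not remove it. The article itself gives repeated observations as the reason for its primary model, and its own schedule contradicts that. A later plan would have to depart from the stated basis, not merely add detail.

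**Conclusion.** The point holds as a contradiction between the stated reason for the primary model and the assessment schedule, together with an unresolved conflict over whether EQ5D is taken at the intervention consultations.

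The consequence depends on which reading is followed:

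- **Interim values used:** the bias runs against the intervention in every null scenario examined. Its size depends on assumed prevalence, correlation and month-6 attendance: about 4 to 23 points at 40% prevalence. It reaches the 13-point target effect in only part of that range.
- **Interim values not used (favoured by the text):** there is no arm-specific bias and no change of endpoint. What remains is a model chosen for a reason that does not apply, where a binary comparison would fit the sample size and the missing-data rule directly.

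The text should be settled before analysis because the first reading could reverse the primary result.

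**What to change.** - Define the primary endpoint in both arms as binary status at 12 months: death, or a severe to extreme level on any EQ5D dimension at the blinded 12-month call.
- State that EQ5D values from intervention consultations are not used for this endpoint.
- Reconcile Intervention Description with Plans for Assessment and Collection of Outcomes on whether EQ5D is collected at the consultations.
- Analyse with the binary methods already named in the article: logistic regression adjusted for age and SOFA with center as a random effect, plus the absolute risk difference from the identity-link binomial model.

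This needs a wording change and no new data. The article says database freezing and analysis are still to come, so it can be made in time. The cost is that timing of deaths leaves the primary test. Mortality remains a secondary outcome, and the article already provides time-to-event methods for it.

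### The prespecified primary model omits pre-ICU EQ5D, a baseline value of the endpoint's own instrument; adding it is a free and probably modest gain in power

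*Protocol article*

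**What the plan says.** Statistical Methods for Primary and Secondary Outcomes names the covariates of the primary piecewise exponential model: "This analysis will be adjusted for age and severity of critical illness (according to SOFA grading", with center as a random effect. Methods for Additional Analyses repeats the same three factors and explains them as predictors of poor outcome and differences in practice between centers.

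Plans for Assessment and Collection of Outcomes says that at inclusion patients were "asked to score their QoL 3 months before ICU admission, using the EQ5D tool". It also says that the MRC, Barthel, IADL, MMS, HADS and IES-R scores and "the social questionnaire were collected for all participants". Intervention Description places randomization after the baseline assessment.

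For continuous outcomes the article says only: "Mixed linear regression will be used for continuous outcomes, possibly after variance-stabilizing transformation". No covariates are listed for these models. The section on nonadherence and missing data announces a detailed SAP, to be written before any analysis.

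**The concern.** The label of the primary endpoint speaks of deterioration in quality of life, but its definition does not refer to the patient's earlier state. A patient with a severe problem in one EQ5D dimension before the ICU is a failure at 12 months unless that problem improves. Where such patients exist, their pre-ICU EQ5D carries information about the outcome that age and SOFA need not carry.

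The value was collected in both arms before allocation, so it is a valid covariate. The article expects the baseline assessment to ensure that the groups are comparable, but measuring a variable does not balance it. Quality of life is also not named as a stratification factor. Leaving it out of the model forgoes whatever power it would have brought, although the data are already in hand.

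**Working it through.** **1. The plan's own size and power.** Inputs from Sample Size: the effect, "powered to detect a decrease from 50% to 37% of patients with very unfavorable outcome"; two-sided alpha 0.05 and 80% power; and the stated result, "the sample size was 249 patients per group".

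With d = 0.13 and mean proportion 0.435, the uncorrected pooled formula is n = [1.96·√(2·0.435·0.565) + 0.8416·√(0.50·0.50 + 0.37·0.63)]² / 0.13², which gives 228 per arm. With the continuity correction it gives 243, which is 2.4% below 249. The stated figure is reproduced to that accuracy. No covariates enter the calculation.

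Power without covariates is Φ{[0.13 − 1.96·√(0.49155/n)] / √(0.4831/n)}:
- n = 249 per arm: (0.13 − 0.0871)/0.0440 = 0.974, power 0.835
- n = 260 per arm (the revised target of 520): 0.851
- n = 273 per arm (546 enrolled): 0.867

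**2. What pre-ICU EQ5D could explain.** The article gives neither the prevalence q of a severe pre-ICU problem nor the failure rate f among such patients. Both are assumed here, with overall failure at 50%. For a yes/no indicator, R² = q(f − 0.5)² / [(1 − q)·0.25], and the equivalent gain in patients is 1/(1 − R²) − 1.

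| q | f | R² | Equivalent extra patients |
|---|---|---|---|
| 5% | 80% | 0.05·0.09/(0.95·0.25) = 1.9% | 1.9% |
| 10% | 80% | 0.10·0.09/(0.90·0.25) = 4.0% | 4.2% |
| 20% | 80% | 0.20·0.09/(0.80·0.25) = 9.0% | 9.9% |
| 20% | 90% | 0.20·0.16/(0.80·0.25) = 16.0% | 19.0% |

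The reference is a model with no covariates. Beyond age and SOFA the gain is smaller to the extent that they overlap with pre-ICU EQ5D.

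**3. The same question in terms of power.** The R² range of 1.9% to 16% corresponds to a covariate-outcome correlation of about 0.14 to 0.40. A logistic simulation used 260 per arm, marginal risks near 50% and 37%, one normally distributed covariate and 2,000 runs per setting. It gave:

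| Correlation | Power, unadjusted | Power, adjusted |
|---|---|---|
| 0.15 | 0.854 | 0.858 |
| 0.23 | 0.838 | 0.867 |
| 0.35 | 0.852 | 0.894 |
| 0.41 | 0.833 | 0.899 |

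Over the assumed range the gain thus runs from almost nothing to about 7 percentage points. The Monte Carlo standard error of each power figure is about 0.008. The simulation is logistic, not the planned piecewise exponential model, so it indicates order of size only. In either kind of model the gain comes mainly from the conditional effect lying further from the null, not from a smaller standard error.

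**4. Continuous secondary scores, for orientation.** Using the inclusion value lowers the standard error by 1 − √(1 − r²). That is 2.0% at r = 0.2, 13.4% at r = 0.5 and 28.6% at r = 0.7. These correlations are also assumed.

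**The case against.** The strongest reply is that the plan is valid as it stands. Randomization protects the analysis with age, SOFA and center, and chance imbalance in other variables is already reflected in the standard error and the type I error rate. The covariate set is short, prespecified and justified. All of this stands, and it limits the point to efficiency.

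The size of the gain is also open to doubt. Eligibility required a McCabe score below 2 and excluded dementia, psychiatric disorder, followed chronic myopathy and an ICU stay in the previous year, so severe pre-ICU problems may be uncommon. The pre-ICU EQ5D is recalled at inclusion, and patients with delirium could be enrolled. The endpoint includes death. Nothing in the article shows that pre-ICU EQ5D is the strongest predictor available. These are reasons to expect a gain toward the lower end of the range, but not to leave the variable out.

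A reader might go further and infer three things that the article does not support:
- **That all continuous secondary models ignore baseline.** No covariates are listed for them, the detail is deferred to a SAP that is not shown, and a mixed model may well use the inclusion value. SF-36 is listed only at 12 months and has no baseline value.
- **That baseline scores serve only to show comparability.** Intervention Description gives a second purpose, to follow the course of impairments in each group.
- **That power is near 80% at best.** On the stated 50% versus 37% it is 0.835 at 249 per arm and 0.867 at 273.

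**Conclusion.** The point holds for the primary model. Its stated covariates omit a pre-randomization measurement on the endpoint's own instrument, and the absolute definition of the endpoint makes that measurement plausibly prognostic. The consequence is lost efficiency. It is not bias, and it leaves the planned size of 249 per arm intact, since that calculation assumed no covariates.

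The loss cannot be computed from the article. Under the assumptions shown, explained variance is about 2% to 16% against no covariates, which is at most some 7 points of power and less once age and SOFA are in the model. A modest gain is the reasonable expectation. For continuous secondary outcomes the protocol contains no error on this point.

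**What to change.** Before database freeze and unblinding, add pre-ICU EQ5D to age, SOFA and center in the primary model. Specify one form in advance: either the weighted score, or an indicator of any severe or extreme dimension. State that missing baseline values will be filled by simple imputation that ignores treatment arm, so that no randomized patient is dropped.

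As a suggestion for the SAP, state whether the inclusion value of the same score enters each continuous secondary model where one exists (MRC, Barthel, IADL, MMS, HADS, IES-R; not SF-36). Take 12 months as the only outcome time, because the 3- and 6-month scores are collected in the intervention arm alone.

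The cost is a sentence or two in the SAP. The data are already collected. According to Results, the database is not yet frozen and the statistician is blinded, so the choice can still be made without knowledge of the results. Made after unblinding, it would be open to the charge of being data-driven.
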